### Objectives {7}

Based on the potential benefits from reducing cumulative prednisolone dose and the possible positive effects of active vitamin D in nephrotic syndrome, the study will test the following hypothesis:
Treatment of MCN with a reduced dose of prednisolone in combination with active vitamin D is non-inferior to standard dose of prednisolone with respect to rate and time to remission.Treatment of MCN with a reduced dose of prednisolone in combination with active vitamin D reduces the incidence of both the observed and subjective adverse events compared with the standard dose of prednisolone.Patients with MCN and a fast turnover of prednisolone have a lower rate of remission, longer time to remission, and fewer adverse events than patients with a slow turnover of prednisolone.

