### Trial design {8}

The trial design is a non-inferior, open-label, randomised, controlled multicentre study including 96 patients with primary, biopsy-proven MCN followed at renal departments in Denmark. The patients are randomised to the following:
Standard prednisolone (1 mg/kg/day, maximum 80 mg/day), orReduced prednisolone (0.5 mg/kg/day) and active vitamin D (alfacalcidol 0.5 μg/day).

When remission is achieved, prednisolone will be taped slowly according to an individual plan (defined by body weight at baseline and the result of randomisation). In both groups, prednisolone will be discontinued 25 weeks after remission. Alfacalcidol will be discontinued at the same time. The patients are followed until first relapse of MCN or for 1 year after remission.

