#### Intervention description {11a}

Patients will be randomised to either standard treatment with prednisolone 1 mg/kg/day or treatment with prednisolone 0.5 mg/kg/day combined with alfacalcidol 0.5 μg/day. The starting dose will remain unchanged until remission of MCN. After remission, prednisolone will be tapered slowly and discontinued after 25 weeks. All trial sites follow the same tapering regimen. The alfacalcidol dose remains unchanged while the patients receive prednisolone and is discontinued along with prednisolone.

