### Assignment of interventions: allocation

#### Sequence generation {16a}

Patients are allocated to the treatment groups at a 1:1 ratio using permuted-block randomisation with random varying block sizes of 4, 6, and 8 stratified by age > 50 years (yes/no). The random allocation list is generated and uploaded to Research Electronic Data Capture (RedCap) by an independent service provider (Clinical Trial Unit, Dept. of Clinical Medicine, Aarhus University) maintaining proper concealment of randomisation.

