### Data collection and management

#### Plans for assessment and collection of outcomes {18a}

The primary outcomes as well as some secondary outcomes are based on blood and urine tests sampled throughout the study period and analysed by using automated and standardised assays by the local Department of Clinical Biochemistry. Patient experienced adverse events are assessed using online questionnaires (SF36 and Cushing QoL) at weeks 2, 6, 10, and 14 before remission, at remission, and at weeks 12, 28, 44, and 52 after remission. Observer assessed, prednisolone-related morbidity is recorded using The Glucocorticoid Toxicity Index [25] reported every 3 months during the follow-up period.

Blood for analyses of genetic variations in the liver enzymes (CYP3A4, CYP3A5, ABCB1, and NR112) will be collected at baseline and stored in a biobank. Unstimulated saliva is sampled after approximately 4 weeks of prednisolone and before dose tapering using a home test (Salivette®). Saliva is sampled five times (0, 2, 6, 12, and 24 h) after taking oral prednisolone. Saliva samples will be stored in the biobank and analysed by liquid chromatography tandem mass spectrometry method in the end of the trial. Concentrations of prednisolone in saliva will be compared to the rate of and time to remission as well as the relapse rate and incidence of adverse events.

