### Statistical methods

#### Statistical methods for primary and secondary outcomes {20a}

The primary endpoints are analysed as intention-to-treat. Since this is an open-label study, there is a risk of cross-over between the two intervention groups, but we expect high adherence to intervention groups. Anyway, additional treated-as analyses will be included. Secondary endpoints are analysed as differences in absolute and relative proportions. Factors affecting the primary endpoint (age, baseline eGFR, albuminuria, prednisolone dose or alternative saliva profile) will be identified using a generalised, linear model.

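### The turnover hypothesis is analysed through saliva concentration with randomised arm left out of the model, so turnover is partly mixed with the treatment contrast

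*Protocol article*

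**What the plan says.** - **Objectives {7}**, third hypothesis: "Patients with MCN and a fast turnover of prednisolone have a lower rate of remission, longer time to remission, and fewer adverse events" than those with slow turnover. The exposure is the patient's own handling of the drug.
- **Outcomes {12}**: one secondary endpoint relates enzyme genotype and the saliva level of prednisolone to remission or relapse.
- **Plans for assessment and collection of outcomes {18a}**: "Concentrations of prednisolone in saliva will be compared to the rate of and time to remission as well as the relapse rate"; the same sentence goes on to adverse events. On timing: "Unstimulated saliva is sampled after approximately 4 weeks of prednisolone and before dose tapering". There are five samples, at 0, 2, 6, 12 and 24 h after a dose.
- **Statistical methods {20a}**: "Factors affecting the primary endpoint (age, baseline eGFR, albuminuria, prednisolone dose or alternative saliva profile) will be identified using a generalised, linear model".
- **Trial design {8}**: "Standard prednisolone (1 mg/kg/day, maximum 80 mg/day", against 0.5 mg/kg/day with alfacalcidol 0.5 μg/day. **Intervention description {11a}** adds: "The starting dose will remain unchanged until remission of MCN".

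No section mentions a clearance, a half-life, a dose-normalised concentration, arm as a covariate or a within-arm comparison. The section on additional analyses {20b} is marked as not applicable.

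**The concern.** Concentration rises with dose and falls with turnover. Before remission the dose is the randomised one, so pooling the arms gives a low concentration two sources: fast turnover, or allocation to the reduced dose. The second source also brings alfacalcidol.

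Adverse events show the problem most clearly. The second hypothesis predicts fewer of them in the reduced-dose arm. The third predicts fewer with fast turnover, that is, with low concentration. If the second is true, a pooled comparison of concentration with adverse events will tend to support the third even if turnover has no effect.

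For an outcome that is alike in the two arms, which is what the trial hopes for remission, the two-fold dose gap adds variation unrelated to the outcome and weakens any true turnover association. Individualised dosing is a declared aim of the trial and rests on this analysis.

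**Working it through.** The plan gives no figure to reproduce here. The check has two parts.

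**1. Share of concentration variance due to arm**

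Inputs: dose ratio 2 (Trial design {8}); 1:1 allocation (Sequence generation {16a}); concentration proportional to dose/clearance (assumption); between-patient log-SD *s* (assumption).

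- Between-arm variance of log concentration: (ln 2 / 2)² = (0.693/2)² = 0.120.
- Share = 0.120 / (0.120 + *s*²).
- *s* = 0.30: 0.120/0.210 = 57%.
- *s* = 0.55: 0.120/0.4225 = 28%.

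Two-fold is an upper bound. The 80 mg cap is stated beside the standard dose, so above 80 kg the ratio falls below 2.

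**2. Effect on a test of concentration**

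Simulation: 43 patients per arm (Sample size {14}), 2000 replicates, logistic model of the outcome on log concentration with and without arm, two-sided 5% test. Assumed: clearance CV 30% or 50% (log-SD 0.29 or 0.47). Standard-arm remission of 80% is from Sample size {14}, and 72% is 0.9 × 80%. The 60% remission rate and the adverse-event rates are illustrative. Entries give the percentage of trials in which concentration is significant, CV 30% / CV 50%.

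| Truth (standard v reduced arm) | Concentration only | Concentration + arm |
|---|---|---|
| No turnover effect, remission 80% v 80% | 4.6 / 4.3 | 4.2 / 4.2 |
| No turnover effect, remission 80% v 72% | 10.0 / 7.5 | 4.9 / 4.4 |
| No turnover effect, remission 80% v 60% | 34.5 / 21.0 | 4.6 / 5.1 |
| No turnover effect, adverse event 60% v 30% | 55.8 / 36.4 | 3.7 / 4.5 |
| True turnover effect (log-odds 0.6 per SD), remission 80% v 80% | 26.7 / 39.0 | 55.4 / 54.9 |

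The first four rows are false positives and the last is power. The Monte Carlo standard error is √(0.05 × 0.95/2000) = 0.5 points near 5%, and about 1.1 points near 50%.

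**Hand check of the dilution.** At CV 30%, *s*² = ln 1.09 = 0.086 and the arm share is 0.120/0.206 = 58%. The true slope per log unit is 0.6/0.294 = 2.04. Without arm it should shrink to about 2.04 × (1 − 0.58) = 0.86. The simulated medians were 0.84 without arm and 2.12 with it.

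**Why arm in the model works.** If the mg/kg dose is constant within an arm, log(dose/concentration) differs from minus log concentration by one constant per arm. An arm term absorbs that constant, so dose normalisation and arm adjustment lead to nearly the same test. They part only through the cap, dose changes, or departures from proportionality.

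**The case against.** The other side has real points.

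- **A reader might infer that the plan commits to unprocessed concentrations. It does not say so.** Statistical methods {20a} says profile, there are five timed samples, the Background says repeated saliva sampling estimates turnover well, and the Discussion says the test is meant to characterise individual pharmacokinetics. A turnover measure could be derived, and the detail could sit in an analysis plan that is not shown. What remains is that Outcomes {12} and {18a} both name concentration as the exposure, and {20a} gives a factor list without arm. The point rests on what is written, not on silence.
- **The dose version of the model nearly contains arm already.** True. Arm is missing in substance when the saliva profile takes the place of dose. Even so, a dose coefficient cannot be separated from alfacalcidol.
- **Concentration may be the right exposure.** For an exposure-response question it could be. The third hypothesis is about turnover, and here the dose contrast is tied to a second drug.
- **It is tempting to say that concentration mostly reflects arm, or that any difference between arms becomes a pharmacokinetic finding.** Neither is supported. Arm explains 28% of variance at the upper assumed SD. The false-positive rate stays near 5% when the arms have equal outcomes and is 8-10% at 80% v 72%.
- **A reader might also infer that about a third of patients remit too early to be sampled.** 1 − 0.2^(4/16) = 33% needs an exponential curve with no lag, whereas remission requires two consecutive tests. The article does not say that early remitters go unsampled. It does ask for sampling at about week 4 and before a taper that starts at remission, so the number without a planned sample should be reported.

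**Conclusion.** The point holds for the turnover hypothesis and for the {20a} model when the saliva profile is used. Done as written, concentration partly stands for arm: about 28-57% of its log variance for an assumed log-SD of 0.55-0.30, with a full two-fold dose ratio and proportional kinetics.

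The consequence depends on the outcome. Where the arms differ, false support for a turnover effect becomes more likely; the 36-56% in the adverse-event example rests on illustrative rates. Where they do not differ, power is lost: 27-39% against about 55% with arm included, for the assumed effect. Adding arm brought the false-positive rate back to about 4-5% in every scenario tried.

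A reader might take this as a threat to the trial's main result. It is not: the primary comparison is by randomised group under intention to treat and uses neither dose nor saliva. The point should be settled before the saliva samples are analysed at the end of the trial.

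**What to change.** 1. For the third hypothesis, name a dose-independent turnover measure from the five timed samples, for example dose/AUC or half-life, and use it in {18a} and in the secondary endpoint in place of concentration.
2. Include randomised arm in every model relating that measure to remission, relapse or adverse events, or analyse within arm and combine. Keep arm in even after normalisation: the Background calls the pharmacokinetics complex and the drug protein bound, so dividing by dose may not remove all dose dependence.
3. In the {20a} model, add arm whenever the saliva profile is used. Dose and saliva may stay as candidate factors.
4. Report the number of patients without a saliva sample by arm and remission status. Starting follow-up at the sample (a landmark analysis) is an optional sensitivity analysis; it leaves out patients already in remission, which must be stated.

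The cost is a change of analysis wording. Allocation, dose and the saliva samples are already planned data, and neither the sample size nor the primary analysis changes.

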#### Interim analyses {21b}

No interim analyses are planned.

#### Methods for additional analyses (e.g. subgroup analyses) {20b}

Not applicable.

#### Methods in analysis to handle protocol non-adherence and any statistical methods to handle missing data {20c}

Missing data will be resolved by carry-over of the last set of recorded data.

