### Outcomes {12}

Remission is defined by a urine-protein/creatinine ratio < 0.4 g/g and/or a urine-albumin/creatinine ratio < 0.3 g/g on two consecutive tests.

Relapse is defined as the recurrence of proteinuria, i.e. a urine-protein/creatinine ratio > 0.75 g/g and/or urine-albumin/creatinine ratio > 0.5 g/g in two consecutive tests and a decline in p-albumin of > 3 g/l.

Primary endpoints:
Rate of remissions after 16 weeks.Time from diagnosis to remission.

Secondary endpoints:
Rate of relapse within 1 year after remission.Time from remission to relapse.Rate of adverse events and number of hospital admissions.The associations between genetic variations in liver enzyme genes, the concentration of prednisolone in saliva, and remission or relapse.

Safety endpoints:
Patient survivalAcute kidney injury (AKI stage 2 or 3 as defined by KDIGO [31])Serious infections requiring admissionPersistent hypercalcaemia (> 2 weeks) defined by an elevated plasma-ionised-calcium and not normalising by reducing alfacalcidol dose.Severe adverse effects to prednisolone, e.g. gastrointestinal bleeding and severe depression

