### Sample size {14}

Based on current data, 80% of patients are expected to achieve remission after 16 weeks of standard treatment [8]. It is considered clinically significant if the remission rate in the low prednisolone + alfacalcidol regimen is less than 90% of the standard treatment regime. Using a non-inferior design with 80% power and a P value of = 0.05, we estimate that 43 patients in each group would need to complete the study. To allow for withdrawals, the study will recruit 96 patients. The incidence of adult MCN in Denmark is 7.3/m/year [4], and with all Danish renal departments participating in the trial, the inclusion is expected to be completed within 4 to 5 years.

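### Carrying the last value forward for all missing data can confirm a remission from one real test and credits relapse-free and event-free time that nobody observed

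*Protocol article*

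**What the plan says.** The missing-data section of the protocol article (item 20c) consists of one sentence: "Missing data will be resolved by carry-over of the last set of recorded data". It singles out no endpoint and exempts no test.

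The Outcomes section (item 12) builds confirmation into both events. "Remission is defined by a urine-protein/creatinine ratio < 0.4 g/g and/or a urine-albumin/creatinine ratio < 0.3 g/g on two consecutive tests". Relapse needs a protein/creatinine ratio above 0.75 g/g and/or a "urine-albumin/creatinine ratio > 0.5 g/g in two consecutive tests and a decline in p-albumin of > 3 g/l". The primary endpoints are "Rate of remissions after 16 weeks" and the time from diagnosis to remission. The secondary endpoints include "Rate of relapse within 1 year after remission" and the time from remission to relapse.

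The statistical methods section (item 20a) analyses the primary endpoints by intention to treat, so filled-in values enter the main comparison. The sample size section (item 14) states that "80% of patients are expected to achieve remission after 16 weeks of standard treatment", sets the limit of concern at 90% of the standard-arm rate, asks for 43 completers per group, and adds: "To allow for withdrawals, the study will recruit 96 patients".

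**The concern.** A second test is required so that one chance low or high value does not decide a patient's outcome. A rule that copies the last recorded set into the next empty slot removes that protection exactly where data are missing. It also treats a patient who has left as one who is still being seen and is unchanged. For the two time endpoints, it supplies event-free follow-up after the last real test, where the usual treatment is to censor.

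This matters more in a non-inferiority trial than in a superiority trial, because errors that blur the arms together work in favour of the claim being tested. The trial is open-label, and its Discussion foresees pressure in the standard arm towards faster dose reduction or cross-over. Missingness unrelated to arm and response therefore cannot be taken for granted.

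**Working it through.** **1. What the rule does to each kind of patient, read literally with the Outcomes section.**

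- First low urine test, next test missed: the low value is copied, the two-test condition is met, and remission is recorded from one real test.
- Lost before any low test: carried as non-remission at week 16, whatever would have happened.
- Lost while in remission: remission values are repeated to 1 year, so no relapse is recorded.
- One high test after remission, next test missed: the copy could confirm a relapse, but only if the required fall in plasma albumin was already on record.
- Time to remission and time to relapse: event-free time continues past the last real test.

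The errors therefore run in both directions.

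**2. The plan's own allowance.** Completers needed: 2 × 43 = 86. Inflating for 10% loss gives 86 / 0.90 = 95.6, rounded up to 96, which reproduces the recruitment target. The implied allowance is 96 − 86 = 10 patients, 10/96 = 10.4%, or 5 of 48 per arm at 1:1 allocation. (The 43 does not follow from the stated inputs. With 80% in both arms, an 8-point margin and one-sided 0.05, the standard formula gives 2 × 0.8 × 0.2 × (1.645 + 0.842)² / 0.08², or 310 per arm. That is a separate matter; 43 is used here only to count the allowance.)

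**3. Weight of one patient.** The limit is 0.90 × 80% = 72%, which is 8 points below 80%. One patient is 1/48 = 2.1 points.

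**4. Outer bound for one arm.** Assume all five allowed losses in an arm lack week-16 status, and 80% of the other 43 remit (34.4 patients). All five counted as failures gives 34.4/48 = 71.7%. All five counted as remissions gives 39.4/48 = 82.1%. The spread is 5/48 = 10.4 points.

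**5. Similar error in both arms.** Let f be the chance that a true non-remitter is recorded as a remission, and g the chance of the reverse. The recorded rate is p(1 − g) + (1 − p)f. With the same f and g in both arms, the recorded difference is (1 − f − g) times the true one, so it shrinks. As an illustration (assumed f = 0.10, g = 0, true rates 80% and 72%), the recorded rates are 82.0% and 74.8%. The difference falls from 8.0 to 7.2 points and the ratio rises from 0.900 to 0.912. That is about one patient per arm (0.10 × 9.6 and 0.10 × 13.4). With g alone the ratio does not move, so on the relative scale of the stated limit the pull comes from false remissions.

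**6. Could the rule alone turn failure into success?** Assume 48 per arm, observed rates of 80% and 72% before misclassification, a Wald interval for the difference, and k reduced-arm patients falsely recorded as remissions with none in the standard arm. The limit to clear is −8 points.

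| k | Difference | Lower limit, one-sided 0.05 | Lower limit, one-sided 0.025 |
|---|---|---|---|
| 4 | +0.3 | −13.1 | −15.6 |
| 5 | +2.4 | −10.7 | −13.2 |

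For k = 4 the standard error is √(0.80 × 0.20/48 + 0.803 × 0.197/48) = 0.0814, and 0.3 − 1.645 × 8.14 = −13.1. Clearing −8 takes seven such patients at one-sided 0.05 or eight at 0.025, more than the five allowed for the arm.

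**The case against.** A reader might infer that, because a 10.4% allowance exceeds an 8-point margin, missing data could swallow the margin and make an inferior regimen pass. The documents do not support this. The allowance covers patients who fail to complete the study, and follow-up runs to first relapse or 1 year after remission. The margin concerns remission at week 16. Anyone who leaves after confirmed remission, or after week 16, has an observed week-16 outcome that carry-over does not touch. Four misclassifications do equal about one margin in the point estimate (4/48 = 8.3 points), but step 6 shows that moving the estimate is not the same as passing the test.

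The event that creates a false remission is also narrow. Loss must fall between the first low test and the confirming one, and the confirming test would have had to be high. Item 11c has the study nurse telephone and rearrange missed visits and tests, and item 18b keeps data from patients who deviate or discontinue unless they refuse.

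The article does not say in so many words that a copied value counts as a second test; one can read the definition as requiring two tests actually performed. Nor does it give a time-to-event method, and a separate analysis plan may state censoring rules and sensitivity analyses. Their absence here is no fault.

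All of this limits the likely size. It does not rescue the sentence, which is a stated rule covering all missing data. Nothing in the article restricts it, and the false-confirmation route exists at any dropout rate.

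**Conclusion.** The point holds as a poorly chosen rule that should be fixed. Read literally, it can confirm a remission from one observed test, count patients lost in remission as relapse-free, and add unobserved follow-up to one primary and one secondary time endpoint. Filled-in values are also treated as observed, which overstates precision.

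The net direction is not fixed. The part that leans consistently one way is a similar false-remission rate in both arms, which favours non-inferiority. The extent is uncertain: the number of patients without week-16 status is not given, and zero to five per arm is an assumed range taken from the whole-study allowance. Within that range, and under the assumptions of step 6, the rule alone does not carry a regimen observed at the limit past the test. It could still add to chance in a single trial. The conclusion rests on reading the rule as applying to the confirming test and to relapse follow-up, which the text does not exclude.

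**What to change.** Replace the sentence in item 20c, before any comparison of the arms, with wording to this effect:

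1. Remission and relapse each require two consecutive tests that were actually performed. No value is carried forward to confirm either event.
2. Time to remission and time to relapse are censored at the last urine test in patients without the event.
3. Missing week-16 remission status is multiply imputed within arm from earlier urine ratios and baseline variables already collected (such as age, eGFR and albuminuria). A sensitivity analysis includes the worst case for non-inferiority: missing in the reduced-dose arm counts as no remission, missing in the standard arm as remission.

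The imputation model and the detail of the sensitivity analysis can sit in the analysis plan; the article needs only to stop prescribing carry-over.

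The cost is wording and modest programming, with no new patients, visits or tests. Intervals widen slightly. If all five allowed losses per arm lacked week-16 status and earlier data told nothing about them, the standard error would grow by √(48/43) = 1.057, about 6%. With fewer losses or informative earlier tests, it would grow by less.
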